**Figure 3 fig3:**
[figure not shown]
Diaphragm ultrasonography1: DE of left and right hemidiaphragm.

In the anterior axillary/mid-axillary line along the rib margins, in B-mode, at a depth of 2–4 cm from the skin, a two-dimensional sagittal image (Figure 4) was obtained, in which a hypoechoic diaphragm located between two layers of hyperechoic lines (pleura and peritoneum) could be seen, and the thoracic and peritoneal spacing perpendicular to the direction of the fibers was measured as the DT (20–22). With the patient’s respiratory movements, the DTei and the DTee can be measured separately. DTR (diaphragm thickening ratio) = DTei-DTee; DTF = (DTei-DTee)/DTee × 100%.

**Figure 4 fig4:**
[figure not shown]
Diaphragm ultrasonography 2: DTei and DTee.

#### Diagnosis to PDD

2.3.2

DE values less than 10 mm or negative (7) [based on our preliminary experiments and others’ studies, the strong association between this critical value and diaphragmatic function has been validated (23)] is our primary measurement. Diaphragmatic weakness is determined where there is decreased DE with or without paradoxical movement during the sniff manoeuver. DTF values below 20% were interpreted as indicative of diaphragm paralysis (9, 13, 24).

### Anesthesia and perioperative management

2.4

#### Anesthesia induction

2.4.1

All patients are transferred to the operation room without any premedication and receive standard monitoring, including electrocardiogram (ECG), noninvasive and invasive blood pressure, peripheral oxyhemoglobin saturation (SpO_2_), respiratory rate (RR), bispectral index (BIS), surgical pleth index (SPI), and partial pressure of end-tidal carbon dioxide (PETCO_2_) intraoperatively. Central venous catheterization is performed in the right internal jugular vein before anesthesia induction. A forced-air warming blanket and core temperature monitoring are routinely used to maintain the patient’s temperature between 36 and 37 °C. Preoxygenation for 5 min, then anesthesia was induced using propofol 1.5–2.0 mg/kg, midazolam 0.08 mg/kg, sufentanil 0.4 μg/kg, and rocuronium 0.9 mg/kg. After artificially assisting respiration for 3 min, all patients were intubated with a Shiley™ double lumen tube to achieve lung isolation and fibreoptic bronchoscopy was used to confirm correct positioning, and then the patient was placed in a supine position or a lateral position, and the fiberoptic bronchoscope was used to check the correct position of the tracheal catheter again.

#### Maintenance of anesthesia

2.4.2

Since there is some influence of anesthesia mode or drugs on diaphragm function, it is important to homogenize the anesthesia management (25). Using PCV-VG mode, two-lung mechanical ventilation sets tidal volume at 6 ~ 8 mL/kg (ideal body weight), with 50%FiO2 to maintain SpO2 ≥ 95% (routine 100% FiO2 avoided to reduce absorption atelectasis risk), and the 50%FiO2 is the minimum feasible concentration to maintain the target SpO2 in this ventilation mode. For one-lung mechanical ventilation, a protective lung ventilation strategy is applied: tidal volume set to 4 ~ 5 mL/kg, respiratory rate adjusted appropriately, PEEP at 3 cmH2O, FiO2 is titrated according to the principle of using the lowest feasible concentration to maintain SpO2 ≥ 90%, and FiO2 titrated to maintain SpO2 ≥ 90% (up to 100% only for persistent hypoxemia), and driving pressure limited to ≤15 cmH2O to ensure PETCO2 ranges 35–45 mmHg. Capnothorax pressure during RATS is maintained at ≤8 mmHg to minimize diaphragmatic compression effects, and after one-lung ventilation completion and before resuming two-lung ventilation, the standardized lung recruitment maneuver technique of sustained inflation is performed for all patients in both VATS and RATS cohorts (sustained inflation at 20–25 cmH2O for 10 s) to reduce atelectasis. Anesthesia was maintained with remifentanil (0.15–0.3 μg/kg/min), propofol (1–4 mg/kg/h) and dexmedetomidine (0.5 μg/kg/h), combined with inhalation of sevoflurane 1–2%, with the anesthetics titrated to maintain a BIS index between 40 and 60 (7, 26) and avoid hypotension or hypertension [defined as a greater than 20% decrease or increase in mean arterial pressure from baseline (27)]. Intermittent intravenous injections of rocuronium are used to maintain muscle relaxation. All patients are managed according to a standardized protocol of enhanced recovery after thoracic surgery.

#### Analgesia and postoperative pain assessment

2.4.3

##### Multimodal analgesia regimen

2.4.3.1

Before the end of surgery, 50 mg flurbiprofen axetil is administered intravenously. At the end of surgery, the surgeon administers intercostal nerve block (site: T3–T7, 0.2% ropivacaine with epinephrine 1:200000, 3–5 mL at each site, using repeat doses) (28); Then a patient-controlled intravenous analgesia (PCIA) pump will be installed. PCIA pump setting: background infusion condition is hydromorphone 0.002 mg/kg/h, the bolus setting is maintained at 0.002 mg/kg, the lockout interval is 10 min (29, 30). When NRS > 4, oxycodone 10-20 mg was administered intravenously to remedy analgesia, twice per day; the standard dose was 20 mg, which was reduced to 10 mg if the patient developed nausea (31). Once the patient’s pain is relieved, perform a diaphragm ultrasound examination on the same day only when NRS ≤ 4. Ondansetron is used to prevent postoperative nausea and vomiting (PONV). Postoperative pain was assessed by the same two physicians throughout the study period using an 11-point numerical rating scale (NRS 0 = no pain; 10 = worst possible pain) immediately after extubation (T1), 1st day after surgery (T2) and 3rd day after surgery (T3), respectively. Additionally, Ramsay sedation scores were performed by the same two physicians at the same time (we incorporated this score into the outcome measurement to clarify whether there is heterogeneity in postoperative sedation levels among the target population and to explore whether or how postoperative sedation levels influence diaphragmatic function or pulmonary outcomes).

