### Study design

2.1

This was a non-randomized, single-center, prospective observational study conducted at the Affiliated Cancer Hospital of Guangzhou Medical University. One hundred and forty-eight patients who underwent elective pulmonary resection for lung disease between July 2025 and May 2026 were included. Figure 1 is the study timeline. Bilateral diaphragm function was monitored by ultrasound at 4 time periods, 1st day before surgery (T0), 30 min post-extubation in the Post-anesthesia Care Unit (PACU) (T1), 1st day after surgery (T2), and 3rd day after surgery (T3). This standardized T1 measurement window will be uniformly applied to all enrolled patients in the study. Diaphragm thickness at the end of inhalation (DTei), diaphragm thickness at the end of exhalation (DTee), and DE during voluntary calming respiration were recorded at each time period. The occurrence of patients’ PPCs was tracked and observed during the 7 day postoperative period, and related clinical variables were recorded, respectively. Figure 2 is the trial flow chart.

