#### Operating process

2.3.1

1st day before surgery (T0), 30 min post-extubation in the Post-anesthesia Care Unit (PACU) (T1), 1st day after surgery (T2), and 3rd day after surgery (T3), diaphragmatic ultrasound was performed with the patient in a semi-recumbent position in bed with the head of the bed elevated by 30° performing quiet breathing. We recorded DE during voluntary calming respiration (7) (excluding deep inspiration and sniff manoeuver, as these two maneuvers are associated with poor compliance in postoperative patients due to pain and chest drain tube interference), we evaluated both left and right hemidiaphragms. To standardize the acoustic window across time points, preoperatively (T0) we mark the probe position on the chest wall using skin-friendly, non-irritating markers, recording the distance from the midclavicular line/anterior axillary line and rib interspace. Postoperatively, if surgical dressings, chest tubes, or subcutaneous emphysema block the original site, we adjust the probe to the nearest adjacent interspace while maintaining the same anatomical orientation relative to the diaphragm dome, documenting the adjustment in the case report form. All diaphragmatic ultrasound measurements at T0–T3 time points are performed by the same fixed team consisting of 1 experienced independent anesthesiologist and 1 resident trainee, both of whom have completed 3 months of specialized training in diaphragmatic ultrasound, to minimize inter-observer variability. The independent anesthesiologist always performed the measurements by first marking the best acoustic window on the patient’s chest for the trainee’s observation of the measurements.

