#### Postoperative extubation

2.4.4

Patients are transferred to the PACU with endotracheal intubation, and 4 mg/kg of sugammadex is intravenously pushed within 10s upon PACU arrival. Extubation will be performed when all the following criteria are met: (1) the patient was fully awake and could perform simple commands; (2) the pharyngeal reflex, swallowing reflex, and coughing reflex were fully restored; (3) the patient’s voluntary respiration was regular, and the tidal volume was 6–7 mL/kg (ideal body weight); (4) SpO_2_ was greater than 96% on FiO_2_ of 0.4 or less and PETCO_2_ was less than 45 mmHg; (5) hemodynamic stability; (6) core temperature was 36.5 °C or higher; (7) no evidence of early surgical complications; (8) adductor hallucis muscle train-of-four ratio (TOFr, T4/T1) ≥ 0.9 (extubation criteria follow international expert consensus or guidelines. However, diaphragm may recover faster than peripheral muscles; a TOFr ≥ 0.9 at adductor hallucis does not fully guarantee complete diaphragmatic recovery. This is precisely the reason why we set up T1–30 min post-extubation for POCUS measurements to ensure as complete a recovery of diaphragmatic function as possible).

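### T1 has two definitions: pain and sedation are scored immediately after extubation but the scan is at 30 minutes, and the NRS ≤ 4 condition cannot always be met in that fixed window

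*Protocol article*

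**What the plan says.** **Scan time.** Section 2.3.1 (Operating process) sets the scan at "30 min post-extubation in the Post-anesthesia Care Unit (PACU) (T1"). Section 2.1 (Study design) adds: "This standardized T1 measurement window will be uniformly applied to all enrolled patients in the study". Section 2.4.4 (Postoperative extubation) gives the reason. A satisfactory peripheral train-of-four ratio does not guarantee that the diaphragm has recovered, and "This is precisely the reason why we set up T1–30 min post-extubation for POCUS measurements".

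**Score time.** Section 2.4.3.1 (Multimodal analgesia regimen) takes the NRS "immediately after extubation (T1), 1st day after surgery (T2) and 3rd day after surgery (T3), respectively". On sedation it says: "Additionally, Ramsay sedation scores were performed by the same two physicians at the same time". One stated purpose of the Ramsay score is "to explore whether or how postoperative sedation levels influence diaphragmatic function or pulmonary outcomes".

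**Rescue and the pain condition.** The same section says: "When NRS > 4, oxycodone 10-20 mg was administered intravenously to remedy analgesia, twice per day". It then makes the scan conditional: "Once the patient’s pain is relieved, perform a diaphragm ultrasound examination on the same day only when NRS ≤ 4". It states no exception for T1.

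**Endpoints.** The primary endpoint (2.7.1) is PDD on postoperative day 1, which is T2. DE, DTF, the T1-to-T0 difference in DE, and the NRS and Ramsay scores are secondary endpoints (2.7.2).

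**The concern.** Two separate things go wrong at T1.

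First, one label covers two moments. A dataset built as written will hold a T1 NRS, a T1 Ramsay score and a T1 excursion that look simultaneous but are about half an hour apart. That half hour is early emergence, when sedation and pain change quickly and an intravenous opioid may be given. An analysis relating T1 sedation to T1 diaphragmatic function would pair the scan with a sedation score from a different state. The Discussion (section 4) says that pain-restricted breathing is hard to tell from true weakness, so pain at the moment of the scan matters for reading T1 excursion.

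Second, the fixed window and the pain condition cannot both hold for a patient whose pain has not come down to 4 by 30 minutes. Without a stated order of precedence, operators may resolve this differently from patient to patient.

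**Working it through.** No figure in the plan is at issue, so the check sets the rules side by side.

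**1. Timeline at T1, taking extubation as minute 0**

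| Item | Time | Source |
|---|---|---|
| NRS, labelled T1 | about 0 min | 2.4.3.1 |
| Ramsay, same time as NRS | about 0 min | 2.4.3.1 |
| Rescue oxycodone 10–20 mg IV if NRS > 4 | after the NRS | 2.4.3.1 |
| Ultrasound, labelled T1 | 30 min | 2.1, 2.3.1, 2.4.4 |

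Gap between scores and scan: 30 − 0 = about 30 minutes, for every patient.

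**2. What the scheduled scores describe, by type of patient**

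- *NRS ≤ 4 after extubation, no rescue.* Both rules are met. The scores are about 30 minutes old at the scan.
- *NRS > 4, rescued, at or below 4 by 30 minutes.* Both rules are met. The scheduled NRS is above 4 while pain at the scan is 4 or below, so the two must differ. The Ramsay score predates the opioid.
- *NRS still > 4 at 30 minutes.* Scanning on time breaks the pain condition, and waiting breaks the uniform window. If no compliant scan is obtained, the value is missing and falls under the multiple imputation in section 2.9. The article does not say which of these should happen.

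**3. Is the conflict specific to T1?** Yes. The condition allows the scan later on the same day. That fits a window defined as day 1 (T2) or day 3 (T3), but not one defined as 30 minutes.

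**4. How many patients?** The documents give no T1 pain data, so both proportions below are assumptions that only show a range. N = 148 is from section 2.8.

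- NRS > 4 right after extubation, assumed 10% to 30%: 148 × 0.10 = 14.8 and 148 × 0.30 = 44.4, or about 15 to 44 patients.
- Of those, still above 4 at 30 minutes, assumed 10% to 30%: 14.8 × 0.10 = 1.5 and 44.4 × 0.30 = 13.3, or about 1 to 13 patients (1.0% to 9.0% of 148).

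The two textual mismatches do not depend on these proportions.

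**The case against.** **The specific rule modifies the general one.** On an ordinary reading, relieving pain first and scanning later that day is an exception to the 30-minute window. A later scan also serves the reason given in section 2.4.4, since the diaphragm has had longer to recover. This is a fair reading and probably what the authors would do. It still contradicts the uniform application in section 2.1, and it sets no limit on the delay.

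**The score timing is one loose phrase in a condensed article.** T1 is defined as 30 minutes everywhere else, and the case report form is not shown. That is possible. But the article states both times explicitly, so this is a disagreement in the text rather than an omitted detail. A sedation score not taken at the scan cannot be recreated in the analysis.

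**The pain condition implies an NRS check at the scan.** This stands. A reader might infer that pain at the scan is never assessed, and the article does not support that. What it does show is that the NRS scheduled as T1 is the earlier one, and that nothing implies a second Ramsay score.

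**The limitations are disclosed.** The Discussion names pain-restricted breathing and possible residual drug effects at T1. Disclosure does not replace scores taken at the scan, which would help in judging the first of these.

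**The loss cannot be put as power.** A reader might infer a definite loss of power for the sedation analysis. The documents do not support one: section 2.9 specifies no test of Ramsay score against excursion, the aim is exploratory, and no correlation is given from which to compute.

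**Conclusion.** Both mismatches are in the text. The score timing matters more, because it applies to every patient: followed as written, the T1 NRS and Ramsay scores describe the patient about 30 minutes before the scan and before any rescue opioid. The exploration of sedation and diaphragmatic function at T1 is weakened, by an amount the documents do not allow one to quantify. The clash between the window and the pain condition is narrower. It concerns only patients above NRS 4 at 30 minutes, whose number is unknown and probably small. The planned intercostal block, flurbiprofen, PCIA and rescue are all meant to keep it so.

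The data touched are secondary: T1 DE, T1 DTF, the T1-to-T0 difference in DE, and the T1 scores when they are related to the scan. A reader might go further and infer that day-1 PDD is compromised, or that the primary result needs relabelling or an added sensitivity analysis. That does not follow. The primary endpoint is at T2, where a same-day delay stays within the window and no second score time is stated.

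The conclusion assumes that the article's stated score time is what is done in practice. If NRS and Ramsay are in fact taken at the 30-minute scan, correcting the wording settles the first part.

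**What to change.** 1. Keep the NRS immediately after extubation as the trigger for rescue, and leave rescue treatment unchanged.
2. Score NRS and Ramsay again at the T1 scan and use those as the T1 values. Give the earlier scores a separate label.
3. Record whether rescue opioid was given before the scan, and the actual scan time.
4. State which T1 rule takes precedence. For example, the NRS condition applies up to a stated maximum delay, after which the scan is done and flagged as taken at NRS > 4.

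The cost is one sentence on timing, a few recorded items and one short extra scoring per patient. There is a trade-off in item 4. Allowing a delay makes the T1 window slightly less uniform, while scanning on time, or at the end of the delay, means a few T1 scans are taken in pain. Either is acceptable if stated and flagged. Enrolment is given as July 2025 to May 2026, so patients already scanned may have only the earlier scores. Those should be reported as post-extubation values and not mixed with scan-time values.

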#### Secondary endpoints

2.7.2

(1) Incidence and severity of PPCs at 7 days postoperatively; (2) T0-T3 diaphragm function at different time points (DTF, DE and the difference of DE between T1/2/3 and T0). (3) NRS scores and Ramsay sedation scores at different time points. (4) QoR-15 scores at different time points.

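### T1 means 30 min after extubation for the ultrasound but the moment of extubation for the pain and Ramsay scores, so the T1 scores cannot reliably show whether sedation or pain influenced the T1 diaphragm reading

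*Protocol article*

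**What the plan says.** For the ultrasound, T1 is consistent throughout the article. The Abstract, Study design (2.1), Operating process (2.3.1), Postoperative extubation (2.4.4) and Discussion (4) all place it 30 min after extubation; in 2.1 the wording is "30 min post-extubation in the Post-anesthesia Care Unit (PACU) (T1"). Study design adds: "This standardized T1 measurement window will be uniformly applied to all enrolled patients in the study". Section 2.4.4 explains that the delay is deliberate, to allow for diaphragmatic recovery after neuromuscular blockade: "This is precisely the reason why we set up T1–30 min post-extubation for POCUS measurements".

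Multimodal analgesia regimen (2.4.3.1) gives a different T1. NRS pain is assessed "immediately after extubation (T1), 1st day after surgery (T2) and 3rd day after surgery (T3), respectively", and "Ramsay sedation scores were performed by the same two physicians at the same time". One reason given for the Ramsay score is "to explore whether or how postoperative sedation levels influence diaphragmatic function or pulmonary outcomes"; another is to see whether sedation levels vary across the study population.

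The same section makes the scan conditional on pain. A patient with NRS above 4 receives rescue analgesia and is scanned that day only once NRS is 4 or lower. Secondary endpoint 3 (2.7.2) is "NRS scores and Ramsay sedation scores at different time points".

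**The concern.** A sedation or pain score can help explain a diaphragm measurement only if it describes the patient at about the time of that measurement. Under the two definitions, a value labelled T1 for Ramsay or NRS and a value labelled T1 for DE or DTF come from different moments in early recovery. Anyone merging the data by time label would treat them as simultaneous.

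The gap matters on the protocol's own reasoning. It delays the scan because the diaphragm is expected to change in those 30 min. Maintenance of anesthesia (2.4.2) states that anesthetic drugs affect diaphragm function. The Discussion names pain-induced splinting and drug-related noise at T1 as difficulties in interpretation, and scores taken with the scan are the data that would help with both. With scores from an earlier state, a real relation would tend to be diluted, and a null T1 finding could be misread as evidence that sedation or pain plays no part.

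**Working it through.** The point rests on comparing the sections; arithmetic only illustrates its possible size.

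**Step 1: the two times side by side.**

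| T1 item | Stated time | Section |
|---|---|---|
| DE, DTF | 30 min after extubation | Abstract, 2.1, 2.3.1, 2.4.4, Discussion |
| NRS | immediately after extubation (about 0 min) | 2.4.3.1 |
| Ramsay | with NRS (about 0 min) | 2.4.3.1 |

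Nominal offset: 30 − 0 = 30 min. No section records a second NRS or Ramsay score as an outcome at the 30 min scan.

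**Step 2: the scan rule.** Suppose a patient scores NRS 7 at extubation. The recorded T1 NRS is 7. Under 2.4.3.1 the patient receives rescue analgesia and is scanned only once NRS is 4 or lower. The T1 DE then belongs to a state with NRS at most 4, after an opioid that may also have changed sedation, possibly more than 30 min after extubation. The rule implies a pain check before scanning, but the article does not say that this value is stored as the T1 score, and there is no matching check for sedation.

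**Step 3: what depends on the T1 scores.** The primary endpoint (2.7.1) is diaphragmatic dysfunction on day 1, which is T2. The sample size (2.8) uses a dysfunction incidence of 30%, a pulmonary complication incidence of 37%, an odds ratio of 3.0, alpha 0.05, power 0.80 and 10% dropout; no T1 score enters. As a check on 148, take 37% as the overall rate, B = 0.30 and a two-sided test. An odds ratio of 3.0 then gives p0 = 0.292 and p1 = 0.553. The formula for logistic regression with one binary covariate gives

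n = [1.96·√(0.37·0.63/0.30) + 0.842·√(p0(1−p0) + p1(1−p1)·0.70/0.30)]² / [(p1−p0)²·0.70] ≈ 129,

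and 129/0.90 = 143.3, so 144. That is within 3% of 148, before any covariate adjustment (its R² is not stated).

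**Step 4: illustration of dilution.** The documents give no correlations, so these are assumptions. Let r be the correlation of the score at the scan with DE, and ρ the correlation between the 0 min and 30 min scores. If the earlier score relates to DE only through the later one, the observed correlation is r·ρ. Approximate power, two-sided 5%, is Φ(atanh(r·ρ)·√(n−3) − 1.96), with n = 148 × 0.90 ≈ 133.

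Example: r = 0.3 and ρ = 0.7 give r·ρ = 0.21, atanh = 0.213, 0.213 × √130 = 2.43, 2.43 − 1.96 = 0.47, and Φ = 0.68.

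| ρ | power, r = 0.3 | power, r = 0.2 |
|---|---|---|
| 1 (score at the scan) | 94% | 64% |
| 0.9 | 88% | 55% |
| 0.7 | 68% | 36% |
| 0.5 | 41% | 21% |
| 0.3 | 18% | 10% |

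The loss is small if the patient's state is stable over the half hour and large if it is not. Nothing in the documents says which.

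**The case against.** The best defence is that this is loose wording rather than a real offset. Study design declares one standardized T1 window for all patients, and the sentence in 2.4.3.1 may simply not have been brought into line with it. The timeline figure, which might settle this, is not available here. That possibility stands, but the text as published gives both times explicitly and has to be reconciled either way.

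Several stronger readings are tempting and do not hold.

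- **That the T1 scores cannot show any influence at all.** An earlier score may correlate with the state at the scan, and the NRS ≤ 4 rule bounds pain at the scan. The supportable claim is that they cannot do so reliably.
- **That secondary endpoint 3 fails at T1.** That endpoint is only the scores over time, which a score at extubation still supplies. The Ramsay score also serves to describe variation in sedation and to relate sedation to pulmonary outcomes; only the diaphragm purpose needs a score taken with the scan. No diaphragm-related purpose is stated for NRS.
- **That all 148 patients are offset by exactly 30 min.** The figure is nominal: the scan may come later in patients needing rescue, and 148 includes the dropout allowance.
- **That moving the Ramsay score would restore its spread.** Extubation requires a fully awake patient, so the spread at 0 min may be narrow. The article does not show that it is wider at 30 min.

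It is also fair that Statistical analysis (2.9) names no T1 analysis of NRS or Ramsay against DE or DTF. The nearest text relates DE reduction to unspecified perioperative variables. The harm therefore falls on an exploratory analysis that the article announces as an aim but does not specify.

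**Conclusion.** T1 has two incompatible definitions. If 2.4.3.1 is followed, the T1 pain and sedation scores are taken nominally 30 min before DE and DTF, longer where the pain rule delays the scan. They cannot reliably show whether sedation or pain influenced the T1 diaphragm reading, and for sedation this undercuts a stated purpose of the Ramsay score.

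The scope is narrow: exploratory analyses at one of three postoperative time points. The T1 scores remain valid descriptions of patients at extubation, and nothing in this inconsistency affects the T2 and T3 scores, the T2 primary endpoint or the sample size. How much the T1 analyses are weakened depends on how stable the scores are over the interval, which the documents do not report; the power figures above are illustrations under assumed correlations. The point is worth correcting because the correction is almost free, not because it threatens the main result.

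**What to change.** Reconcile 2.4.3.1 with 2.1, 2.3.1 and 2.4.4.

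1. Record NRS and Ramsay at the T1 scan, 30 min after extubation, and use those values in any T1 analysis involving DE or DTF.
2. Keep the score at extubation under a separate label. It should not be dropped: the scan rule truncates NRS at the scan at 4, so only the extubation score can record higher pain. The same truncation limits what the scan-time NRS can show about pain and DE, and the report should say so.
3. Enrolment runs from July 2025 to May 2026. For patients already enrolled, use the actual score and scan times where available and state the offset alongside any T1 result.
4. If scoring was in practice already done at the scan, correct the sentence in 2.4.3.1; steps 1 and 3 then need no further action, and there is no separate extubation score to keep.

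The cost is one sentence, one additional time label on the case report form and one extra short assessment by the same two physicians with the same scales. Sample size, visits and the primary analysis do not change.
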